### Ethics

The Medical Ethical Committee of Erasmus Medical Center, Rotterdam, the Netherlands, has approved this study, registered under NL38571.078.12.

### Participants and eligibility criteria

The target group consists of adult patients (18+) with BPD, consecutively referred for treatment by general practitioners, mental health care institutions, private practices and general hospitals.

#### Inclusion criteria for MBT treatment and for this study

Inclusion criteria are (a) a BPD diagnosis as assessed using the Structured Clinical Interview for DSM-IV Axis II Personality Disorders (SCID-II) [39], (b) 18 years or older, (c) adequate mastery of the Dutch language and (d) travel time to the MBT setting less than 1 hour.

#### Exclusion criteria for this study

Exclusion criteria for MBT are kept to a minimum because the treatment aims to reach a broad population of BPD patients. In this study, only patients with (a) a diagnosis of autism spectrum disorders, chronic psychotic disorder or organic brain disorder that interferes significantly with the ability to mentalize; (b) intellectual impairment (IQ <80 as measured by the Wechsler Adult Intelligent Scale–III) [40]; or (c) a diagnosis of antisocial personality disorder in combination with a history of severe physical violence are excluded. In addition, patients who have had a stable job for a period of at least 2 years for a minimum of 15 hours a week, and/or are caregivers with main responsibility for children under 4 years of age, are allowed to participate in the randomized study at their own choice. Because of ethical reasons (i.e. randomization to MBT-DH cannot be combined with a job or being the main carer for children because of the fixed time commitment involved), these patients were not seen as refusers, and were given the option to enter MBT-IOP directly.

### Procedure

All patients referred to one of the mental health care centres are invited for a standard intake interview, which includes standardized assessment by means of the Structured Clinical Interview for DSM-IV Axis I disorders (SCID-I) [41] and SCID-II [39]. All patients eligible for MBT treatment (with a BPD diagnosis and aged ≥18 years) are given both written and verbal information about the study. Eligible patients are given 1 week to consider participation in the trial. Patients who are willing to participate in the study are asked to sign an informed consent sheet and complete the baseline assessment. Next, they are randomized to either MBT-DH or MBT-IOP by an independent researcher using a computerized 1:1 algorithm. Patients are informed about their treatment allocation and placed on a waiting list. One week prior to start of the main treatment phase, and subsequently at 6-months intervals up to 36 months after the start of treatment, patients complete an assessment battery as described below. Patients who are excluded from the trial on the basis of exclusion criteria, or who refuse to participate in the trial, are ideally assigned to an alternative evidence-based treatment. Excluded and refusing patients are asked to complete the baseline assessment only, for which they sign a separate informed consent form. At 18 and 36 months, the SCID-I and SCID-II are re-administered by MSc-level psychologists. Extensive efforts are being made to collect data at the follow-up time points by means of an outreaching approach towards patients: patients are contacted by telephone, e-mail and letters (with reminders as necessary) to motivate them to attend assessments, and home visits are made if necessary.

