## Methods/design

### Design

This study is a multisite RCT comparing the efficacy and cost-effectiveness of MBT-DH versus MBT-IOP in the treatment of BPD (see Figure 1). Patients are randomly allocated to either MBT-DH or MBT-IOP and assessed before randomization, before start of treatment and subsequently every 6 months up to 36 months after start of treatment.

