#### Pretreatment

Patients enter the pretreatment programme until a place becomes available in the treatment to which each patient has been randomized (MBT-DH or MBT-IOP). For both MBT-DH and MBT-IOP the pretreatment programme focuses on engaging the patients in treatment and crisis management. It consists of an introductory course to MBT (MBT-I), and biweekly individual sessions with crisis planning as focus. MBT-I is an explicit mentalizing group with a psychoeducational element, which is considered an important part of the programme. The programme consists of 12 highly structured sessions that stimulate patients to consider the overall process of mentalizing and its relation to their problems, and how these problems will be addressed in MBT [25,42].

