### Statistical analyses

First, to investigate potential differences between the two groups at baseline, we will use parametric and nonparametric descriptive statistics, as appropriate. For the main analyses concentrating on primary and secondary outcomes, linear growth curve models for normally distributed outcome measurements will be used, logistic regression for binary data, and Poisson regression models for ordinal data. Results will be expressed in terms of comparison of the slopes for interval data, odds ratios for binary data, and incidence rate ratios for ordinal data. Furthermore, we will perform explorative analyses regarding predictors of differential treatment outcome. All analyses will be conducted according to intention-to-treat principles.

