#### Health economic evaluation

We will estimate the difference in total costs for MBT-DH compared to MBT-IOP and the difference in clinically relevant effects of the treatments. By dividing the difference in costs by the difference in effectiveness, the incremental cost-effectiveness ratio (ICER) will be estimated. The ICER represents the extra amount of money that has to be invested to gain one extra unit of effect (or, conversely, the amount of money that will be saved if one unit of effect is lost).

In the economic evaluation, all relevant costs and effects will be taken into account. This means that we will use a so-called societal perspective, which is preferred in economic evaluations in the Netherlands [82]. The costs will include *all* costs, that is, intervention costs, direct and indirect medical costs, as well as productivity losses and costs accruing elsewhere in the health care system. From the societal perspective, clinically relevant effects are those effects that are meaningful for society. Moreover, in order to be able to compare effects between different interventions in health care, effects should be expressed in generic terms. We will therefore use QALYs and will express the cost-effectiveness of each intervention and the ratio between these cost-effectiveness estimates as cost per QALY. The use of QALYs is advised in guidelines for cost-effectiveness analysis, especially when main effects are expected in quality of life [82,83].

Our primary cost-effectiveness ratio will be estimated using empirical data only and therefore a 3-year time horizon will be used, which is equal to the trial duration. Cost data are generally highly skewed, and QALY scores and ICER values are not distributed normally in most cases. Therefore, the uncertainty intervals around the mean costs, mean effects and mean ICER values will be estimated using bootstrap simulations with at least 1000 replications [84-86]. These results will be graphically presented in a cost-effectiveness plane. Various societal willingness-to-pay values will be used to estimate net monetary benefits. These net monetary benefits are then used to derive cost-effectiveness acceptability curves.

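### Follow-up is dated from treatment start, after randomization and an open-ended pretreatment wait, so never-starters have no datable visits and the 3-year horizon leaves out the wait

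*Protocol article*

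**What the plan says.** In the Procedure section, consent and the baseline assessment precede randomization. After randomization, "Patients are informed about their treatment allocation and placed on a waiting list". The remaining assessments are tied to treatment: "One week prior to start of the main treatment phase, and subsequently at 6-months intervals up to 36 months after the start of treatment". The Design section gives the same schedule in short; patients are "assessed before randomization, before start of treatment and subsequently every 6 months up to 36 months after start of treatment".

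The Pretreatment section describes what fills the gap: "Patients enter the pretreatment programme until a place becomes available in the treatment to which each patient has been randomized". It gives no maximum or expected length. The gap is not an empty wait. Of the pretreatment programme it says: "It consists of an introductory course to MBT (MBT-I), and biweekly individual sessions with crisis planning as focus". MBT-I alone has 12 sessions. The Treatments section, by contrast, presents MBT-I as the opening of treatment itself.

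The Sample size section plans on seven repeated measures, with a correlation between a baseline and the last follow-up, and does not say which assessment is that baseline. The Statistical analyses section promises: "All analyses will be conducted according to intention-to-treat principles". For the primary cost-effectiveness ratio, the Health economic evaluation section says that "a 3-year time horizon will be used, which is equal to the trial duration".

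**The concern.** Randomization makes the arms comparable at one moment, the moment of allocation. Whatever happens afterwards, including how long a patient waits and whether the patient starts at all, may be a consequence of the allocated arm. A follow-up clock that starts later raises three problems.

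- **Missing visits.** The visits of randomized patients who never start cannot be dated, and a later analysis plan cannot recover data that were never due.
- **Baseline.** If the value at treatment start served as baseline, it would be measured after patients knew their arm and had received part of the programme.
- **Economics.** Health and resource use during the wait follow from allocation, yet a horizon that begins at treatment start leaves them out.

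The article gives reasons why the arms might differ here. Places are specific to the arm. One programme takes five days a week and the other is outpatient. The exclusion criteria section says that the day hospital cannot be combined with a job or with being the main carer of children, yet lets such patients be randomized if they choose. They learn their arm before they start.

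**Working it through.** T0 below is the pre-randomization assessment. T1 is the assessment at start of treatment, a label the article uses in its Trauma section.

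**1. Order of events (Procedure, Pretreatment).** T0, randomization, disclosure of arm, waiting list with pretreatment, T1 one week before main treatment, main treatment, then visits at 6 to 36 months. For a patient who never enters main treatment, the date of each visit (start + 6, ..., start + 36) has no value. T1 has no date either, so the trauma questionnaire, which is given only at T1, is lost as well. The outreach described in Procedure has no due date to work to.

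**2. Number of measures.** The Abstract lists one before randomization, one at start of treatment, and 6, 12, 18, 24, 30 and 36 months: 1 + 1 + 6 = 8. The Sample size section uses 7. Two readings give 7: T0 plus six follow-ups, or T1 plus six follow-ups. Procedure uses the word baseline for the pre-randomization assessment, which favours T0. The follow-up clock favours T1. The count alone cannot decide.

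**3. Meaning of treatment start.** Procedure ties it to the main treatment phase. Treatments says that treatment opens with MBT-I, which the Pretreatment section places before the main phase. On the second meaning the 36 months would begin earlier. These passages must be reconciled.

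**4. Horizon.** With a wait of w months, randomization to last visit is 36 + w, and the share before the clock starts is w / (36 + w). The documents give no w, so the values are assumed:

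| Assumed wait (months) | Randomization to last visit (months) | Share before the clock starts |
|---|---|---|
| 0 | 36 | 0% |
| 3 | 39 | 3/39 = 7.7% |
| 6 | 42 | 6/42 = 14.3% |
| 12 | 48 | 12/48 = 25% |

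Three years equals the trial duration only if w = 0 or if time is counted from treatment start. A horizon of 36 months from randomization would stop w months before the last visit.

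**5. What can be valued during the wait (Costs).** The cost questionnaire is given at a baseline that is not identified and then at 6, 12, 18, 24 and 36 months. Direct costs are measured per 4 weeks. No visit falls between T0 and T1, so costs and QALYs over the wait would have to be interpolated.

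**6. Loss of never-starters (illustration).** Suppose never-starters fare g SD worse than starters in both arms, and their share differs by Δp between arms. Leaving them out shifts the difference in means by Δp × g.
- Δp = 0.15, g = 0.5: 0.15 × 0.5 = 0.075 SD.
- Δp = 0.20, g = 1.0: 0.20 × 1.0 = 0.20 SD, which is 0.20 / 0.5 = 40% of the planned 0.5 SD.

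**7. Unequal waits (illustration).** The Sample size section gives a within-group effect of 1.31 SD for MBT-IOP. Spread over an assumed 18 months, this is 1.31 / 18 = 0.073 SD per month. If waits differed by 3 months and pretreatment worked at half to all of that rate, the arms would differ at T1 by 0.11 to 0.22 SD. This is a difference in level at T1. It is not a bias of that size in a slope.

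The planned 45 per group enters none of these steps.

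**The case against.** The strongest reply is that the article never states the harmful steps, and much of it stands.

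- **A reader might infer that the growth curve starts at T1.** Statistical analyses gives no time zero, and the seven measures fit T0 equally well. T0 as baseline may already be intended.
- **A reader might infer that never-starters are excluded and intention-to-treat is broken.** No section excludes them. Analysis by allocated arm remains possible, every randomized patient should have a T0 value, and a model that includes T0 can keep patients with incomplete follow-up. What the text supports is narrower: these patients have no scheduled outcome after randomization.
- **A reader might infer that the cost of pretreatment sessions is left out.** The Treatments section makes pretreatment the first phase of both programmes, and the economic sections promise intervention costs and all other costs. The sessions may well be counted. The remaining gap is QALYs and non-intervention costs during the wait.
- **A reader might infer that the effect is biased by up to 0.2 SD.** Pretreatment is described alike for both arms, allocation is 1:1, and six groups are offered in each arm. Equal numbers of groups do not guarantee equal waits, but the documents contain no evidence of unequal waits or unequal non-start. In an analysis of slopes from T1, the level difference in step 7 would go into the intercept.

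Dating visits from treatment start is also a reasonable choice in a trial with a waiting list, because it lines visits up with the treatment phases. And an article may leave visit-dating detail to a fuller document. None of this supplies a date for a never-starter's visits, or makes three years equal to the trial duration when patients wait.

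**Conclusion.** The point holds as a gap in the schedule and in the horizon, with bias as a risk that has not been shown. Three things are established from the text:

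- As written, never-starters have no datable visit at 6 to 36 months, although intention-to-treat is promised for all analyses.
- The statement on the 3-year horizon fits only a clock that starts at treatment start. It then leaves out QALYs and non-intervention costs during the wait, which is 7.7% to 25% of the time from randomization to last visit for assumed waits of 3 to 12 months.
- The planning baseline and the meaning of treatment start are not settled.

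The SD figures in steps 6 and 7 rest on assumed differences in non-start, prognosis and waiting, and show only what such differences could do. The stronger conclusion, that the trial compares only patients who started, is not supported. This is an inexpensive improvement that protects the randomized comparison.

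**What to change.** 1. Name the T0 value as baseline in all outcome models and treat T1 as a post-randomization measure. Say which seven of the eight assessments the power calculation used.
2. Date the follow-up of never-starters from randomization, for example by adding the median wait at the site to randomization before the 6-month steps. Collect it through the outreach already described.
3. Run the cost and QALY horizon from randomization, including pretreatment sessions and the waiting period, and correct the statement that three years equals the trial duration.
4. Reconcile the passages on when treatment starts, and keep the analysis from treatment start as a supplement.

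The cost is a few extra follow-up contacts, some interpolation of costs and QALYs over the wait, and visits unevenly spaced from randomization, so that actual dates must enter the models. T0 is already collected. Recruitment ended in June 2014, so item 2 can reach only visits still to come. Items 1 and 3 define the analysis and can be fixed at any time before outcomes are analysed.

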### Treatments

MBT was developed by Fonagy and Bateman in the United Kingdom [3,24,25,42]. The term *mentalizing* refers to the ability to attend to mental states in ourselves and in others as we attempt to understand our own actions and the actions of others on the basis of intentional mental states. The aim of MBT as a therapy is to help patients develop an increasingly robust mentalizing process within the context of interpersonal interactions. Treatment begins with MBT-I, an introductory phase with psychoeducational elements. This is followed by a combination of individual and group therapy.

MBT works through continuously helping the patient to maintain or re-establish a mentalizing process while simultaneously stimulating the attachment system by balancing the level of optimal arousal. With a main focus on current rather than past experience, patients are encouraged to explore the mental states of themselves and others, to become curious about alternative perspectives, to find out more about how they think and feel about themselves and how this influences their behaviour, and how distortions in understanding themselves and others lead to problems in interpersonal functioning. The exploration and identification of emotions within multiple contexts, particularly interpersonal contexts, promotes the development of secondary representations to primary affective experiences. This enhances affect regulation and the development of a coherent sense of self. These elements form key components of mentalizing capacity. In this manner, the work in therapy addresses BPD patients' difficulties with affect, impulse regulation and interpersonal functioning. Destructive behaviour, which from an MBT perspective is understood as an attempt to maintain a sense of stability and manage incomprehensible feelings in the absence of a mentalizing capacity, is reduced as a consequence of the development of this capacity. Another important focus lies in generalizing improvements in daily life to wider social functioning. Thus, by means of improving patients’ mentalizing capacity, several domains of functioning are addressed.

Both MBT-DH and MBT-IOP have five general treatment goals: (1) engagement in therapy; (2) reduction of psychiatric symptoms, particularly depression and anxiety; (3) reduction of self-damaging, threatening or suicidal behaviour; (4) improved social and interpersonal functioning; and (5) stimulation of appropriate use of general mental health services (including prevention of reliance on prolonged hospital stays). Goals are personalized and linked to the components of the programme. Both MBT programmes are divided into three phases: (1) pretreatment, (2) main treatment, and (3) follow-up treatment [3,24,25,42].

#### Pretreatment

Patients enter the pretreatment programme until a place becomes available in the treatment to which each patient has been randomized (MBT-DH or MBT-IOP). For both MBT-DH and MBT-IOP the pretreatment programme focuses on engaging the patients in treatment and crisis management. It consists of an introductory course to MBT (MBT-I), and biweekly individual sessions with crisis planning as focus. MBT-I is an explicit mentalizing group with a psychoeducational element, which is considered an important part of the programme. The programme consists of 12 highly structured sessions that stimulate patients to consider the overall process of mentalizing and its relation to their problems, and how these problems will be addressed in MBT [25,42].

#### Main treatment

##### MBT-DH

MBT-DH is an intensive, manualized treatment for patients with BPD. It has been described in detail elsewhere [3,33]. Briefly, MBT-DH consists of a highly structured day hospitalization programme with a maximum duration of 18 months, covering five days per week. MBT-DH consists of the following components: daily group psychotherapy, weekly sessions of individual psychotherapy, individual crisis planning on indication (average: weekly for 3 months and from then on lower in frequency), art therapy twice a week, mentalizing cognitive group therapy, and writing therapy. Each week’s programme is ended with a social hour and a community meeting. Patients in the MBT-DH programme can also consult a psychiatrist upon request and medication is prescribed following American Psychiatric Association (APA) guidelines [15].

##### MBT-IOP

The main treatment phase in MBT-IOP consists of group psychotherapy twice a week, weekly sessions of individual psychotherapy, and individual crisis management on indication (average: weekly for 3 months and from then on lower in frequency). Patients can also consult a psychiatrist upon request and medication is prescribed following APA guidelines.

#### Follow-up treatment

For patients in either treatment condition, the final phase of the programme offers individually tailored stepped-down care aiming at relapse prevention, maintaining and further enhancing the gains made in mentalizing capacity, and stimulating further rehabilitative change and reintegration into society.

### Therapists

Both the MBT-DH and MBT-IOP teams consist of therapists with broadly ranging level of experience, background, and educational level. All therapists involved in the study are certified psychologists, psychotherapists, psychiatrists, nurses or art therapists. All clinicians who are involved in the study have successfully completed a certified MBT basic course, after which they receive continuous supervision in working with the MBT model.

### Treatment adherence

One of the authors, [name], trained by [name], was involved in the implementation and monitoring of MBT at the different treatment sites. Adherence to the MBT treatment model is monitored in several ways. First, adherence in daily practice is monitored by means of reflections after each group therapy session, in which therapists are continuously stimulated to reflect on their adherence to the treatment model. Specifically, therapists are asked to reflect on whether their interventions have enhanced mentalizing which interventions have not achieved this, and what alternative interventions might have been more successful. Second, within both the MBT-DH and the MBT-IOP programme, biweekly team supervision focuses on review of case material to increase therapists’ comprehension of mentalizing theory and their competency in working with the principles of MBT and the spectrum of mentalizing interventions. Third, we will rate the adherence to the model of both group and individual sessions using videotaped sessions. Based on the videos, raters trained in the use of the Adherence and Competence Scale [43] will measure therapist adherence.

